#### Clinical variables

At inclusion the following information will be collected (variables included as independent variables in the primary analyses are denoted with an asterisk): Age^*^, gender^*^, ethnicity, height, comorbidity^*^ (Charlson Comorbidity Index) [51], Karnofsky performance status^*^ [52], living situation, educational level, alcohol use, smoking status^*^, type of department (palliative care unit, surgical ward, general oncology ward, out-patient clinic, other), oncological history related to the current cancer disease (tumor diagnosis^*^, time since cancer diagnosis^*^, presence of metastases other than bone^*^, osteolytic metastasis at each planned site for RT^*^, soft tissue expansion at each planned radiation site^*^, previous and on-going anti-cancer treatment: (RT, surgery, chemotherapy, hormonal treatment, other interventions – for the primary analyses current oncological treatment other than RT (Y/N)^*^), planned RT (fractions^*^, total dose^*^ and anatomical region; narrow to radiation location in weight bearing bone (Y/N) for the primary analyses^*^, re-irradiation, previous pain treatments (duration of opioid treatment and previous unsuccessful trials with other opioids) and medications and doses for the previous 24 h (for the primary analyses we will include opioid dose in oral morphine equivalents last 24 h^*^and steroids^*^). In addition, an objective measurement of lean body mass, measured by CT scan of L3 and/or Th4 vertebrae will be performed at baseline.

At both baseline and at all follow-up visits the following self-reports will be collected: Health related quality of life (EORTC QLQ-C15 PAL) [53] (for the primary analyses trouble sleeping^*^, nausea^*^ and constipation^*^ will be included as variables), nutritional status (PG-SGA) [54], weight, overall and site specific average and worst pain last 24 h (BPI) [55] (for the primary analyses “worst pain last 24h”^*^), pain at rest and at movement from each planned irradiated site [56] (for the primary analyses we will use the variable that reflects worst pain at the irradiated site at baseline^*^) and depression^*^ (PHQ9) [57]. Specific questions related to episodic pain^*^ and self-report neuropathic symptoms and signs^*^ (LANSS) [58] will be asked at baseline and after 3 and 8 weeks.

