Data on history of hospitalizations, changes in medications, new cancer treatment, treatment for hypercalcemia, new pathological fractures or spinal cord compression since last visit will be obtained at all follow-up visits (Table 1).

**Table 1 Tab1:** Flow chart for registrations

	Time of assessment					
	Inclusion	3 W	8 W	16 W	24 W	1 YR
Screening for inclusion	X					
Demographics, cancer history, planned RT, previous pain therapy	X					
New cancer related incidents		X	X	X	X	X
Current use of medications	X	X	X	X	X	X
Weight	X	X	X	X	X	X
Performance status	X	X	X	X	X	X
CT scans for body composition (if available)	X	X	X	X	X	X
PG-SGA	X	X	X	X	X	X
Pain registrations	X	X	X	X	X	X
QLQ-C15 PAL	X	X	X	X	X	X
LANSS	X	X	X			
Episodic pain questions	X	X	X			
PHQ9	X	X	X	X	X	X
Blood samples for clinical chemistry	X	X	X	X	X	X
Blood samples for biomarkers	X	X	X	X	X	X
Blood samples for genetics	X					

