*Outcome*: Cachexia is defined as a) weight loss > 5% over past 6 months (in absence of simple starvation); or b) body mass index (BMI) < 20 and any degree of weight loss > 2%; or c) appendicular skeletal muscle index consistent with sarcopenia (males < 7・26 kg/m2; females < 5・45 kg/m2) and any degree of weight loss > 2% [38]. Cachexia severity is assessed as degree of weight loss and EORTC QLQ C15 PAL physical function and appetite loss.

*Statistical method*: Fist, we will perform a cross-sectional analysis in the baseline parameters using a logistic regression with cachexia as outcome, and the various inflammatory markers as explanatory variables. Second, we will investigate the association between changes in inflammatory markers over time and cachexia severity using mixed linear modelling.

**Research question 4:** Which inflammatory substances are associated with depression in cancer patients?

*Objective*: To explore the associations between serum concentrations of inflammatory substances and depression.

*Outcome*: Depression is measured by the PHQ-9 questionnaire [57]. The PHQ-9 includes 9 items identical to the diagnostic criteria (i.e. the depression symptoms) for depression disorder. For the purpose of these analyses we will use depressive disorder as defined by the PHQ-9 recommended sum score calculation, and symptom by symptom in the PHQ-9 score in associations of serum concentrations of inflammatory biomarkers during a period of 1 year form inclusion.

*Statistical method*: We will use repeated measurements and a linear mixed effect model to perform the analyses.

**Research question 5:** Which are the clinical predictors and biomarker predictors of development of cachexia in patients with metastatic cancer disease?

*Objective*: To obtain demographic and clinical data and biomarkers in a homogenous population of patients with metastatic cancer, and within a prospective, longitudinal follow-up study observe which factors predicting the development of severe cachexia during one-year follow-up.

*Outcome*: Cachexia is defined as for research question 3.

*Statistical method*: As the purpose is to evaluate development of cachexia, only patients without cachexia at baseline will be included in this analysis. A Cox regression will be used to evaluate baseline predictors of cachexia development.

**Research question 6**: What is the relationship between pain reduction and depression in patients receiving RT for CIBP?

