### Ethics

A signed consent will be obtained from all participants by an investigator at each site. The study will be carried out in accordance with ICH GCP and the World Medical Association Declaration of Helsinki (1964) and its’ revisions (Tokyo 1978, Venice 1983, Hong Kong 1989, South Africa 1996 and Edinburgh 2000). The study is approved by The Regional Committee for Medical and Health Research Ethics, REC Central Norway, and by the regulatory authorities at each trial site. If modifications to the protocol, amendments will be applied for to the regional ethics committee and after approval distributed to all local study investigators.

RT is indicated and will be given regardless of whether the patients choose to participate in the study or not. Thus, study participation means that patients consent to report symptoms and have their blood drawn. The volumes of blood samples are limited (less than 50 ml) and give no extra risk for anemia. Thus, the study includes no interventions that increase the risk for the patients. Data are handled anonymously. The database used for analyses only identify each patient by a study number. The linkage between study number and patient identity is in a document and / or memory stick stored in a safe at each study center.

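### Cachexia criterion (c) needs a limb-muscle index for which the article lists no measurement, so it cannot be applied as written in research questions 3 and 5

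*Protocol article*

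**What the plan says.** Research question 3 (Protocol article, Outcome and statistical analyses) counts a patient as cachectic if any one of three criteria is met:

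- (a) "weight loss > 5% over past 6 months (in absence of simple starvation";
- (b) "body mass index (BMI) < 20 and any degree of weight loss > 2" per cent;
- (c) "appendicular skeletal muscle index consistent with sarcopenia", with cut-offs "males < 7・26 kg/m2; females < 5・45 kg/m2", again together with weight loss above 2%.

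This yes/no definition is the outcome of the baseline logistic regression in question 3. Question 5 takes it over, admits only patients free of cachexia at baseline, and models later cachexia with Cox regression. The second, longitudinal analysis of question 3 uses severity instead: degree of weight loss and two QLQ-C15 PAL domains.

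On measurement, the Clinical variables section says that "an objective measurement of lean body mass, measured by CT scan of L3 and/or Th4 vertebrae will be performed at baseline". Table 1 has a row "CT scans for body composition (if available", marked at inclusion and at all five follow-up visits. The Ethics section says that "study participation means that patients consent to report symptoms and have their blood drawn".

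The objective of question 5 refers to "the development of severe cachexia during one-year follow-up". Its question, outcome and method refer to cachexia without that qualifier.

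**The concern.** A diagnostic criterion must be computable from what is collected. Criterion (c) asks for limb muscle mass per height squared, while the scans listed are of the trunk at vertebral level. The analyst will have to drop (c) or put something in its place, and the article does not say which.

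The choice matters most in question 5, where the definition sets both who enters the Cox model and what counts as an event. If a CT-based stand-in is used and CT exists only for some patients, cachexia status depends partly on whether a scan was done. The severe/any wording adds a second ambiguity about the same event. If both are left open, they will be settled after the data have been seen.

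**Working it through.** The document gives no cachexia rate, no CT coverage and no sample size for questions 3 or 5, so there is no figure of the plan to reproduce. Its one sizing rule (10 x 29 = 290, Power consideration) concerns response to RT. The check is therefore one of consistency, followed by a bound.

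**Step 1. Can each criterion be computed?**

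| Criterion | Needs | Listed in the article |
|---|---|---|
| (a) | weight loss over 6 months | weight at every visit |
| (b) | BMI and weight loss | height at inclusion, weight at every visit |
| (c) | appendicular muscle index in kg/m2 and weight loss | CT at L3 and/or Th4; no limb measurement, no conversion, no CT cut-off |

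The article does not itemise weight before inclusion. All three criteria need it for baseline weight loss, so it does not set (c) apart. The muscle index does.

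**Step 2. Is CT there for everyone?** At baseline, Clinical variables states it without condition and Table 1 makes it conditional. That is a contradiction. At follow-up, the conditional entry in Table 1 is the only statement. The Ethics description of participation names no study imaging.

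**Step 3. Whose status can (c) change?** Take weight loss over the same window and leave aside the starvation exclusion in (a).

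- Loss of 2% or less: no criterion is met.
- Loss above 5%: (a) decides.
- Loss above 2% and up to 5%, BMI below 20: (b) decides.
- Loss above 2% and up to 5%, BMI 20 or more: only (c) can decide.

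Only the last group is exposed.

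**Step 4. What could happen to that group?** The article allows at least three readings.

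- (c) is dropped: everyone is classified alike, but not by the stated definition.
- A CT surrogate is used and patients without CT are left out: the analysis is restricted to scanned patients.
- A CT surrogate is used and no CT counts as not sarcopenic: true (c)-only cases without a scan are called non-cachectic. In question 3 they are false negatives at baseline. In question 5 they enter the risk set as prevalent cases, and their event depends on a later scan or on meeting (a) or (b). New (c)-only cases without a scan are missed or dated late.

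**Step 5. Illustrative size under the third reading.** Share missed at baseline = w x s x m, where w is the share of patients in the exposed group, s the share of those who are truly sarcopenic, and m the share without a usable scan. All three are assumptions, none from the document: w 5% to 25%, s 20% to 50%.

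| m | Low (w 5%, s 20%) | High (w 25%, s 50%) |
|---|---|---|
| 0% | 0 | 0 |
| 30% | 0.05 x 0.20 x 0.30 = 0.3%; 1.8 of 600 | 0.25 x 0.50 x 0.30 = 3.75%; 22.5 of 600 |
| 60% | 0.6%; 3.6 of 600 | 7.5%; 45 of 600 |
| 100% | 1.0%; 6 of 600 | 12.5%; 75 of 600 |

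Question 5 excludes patients with baseline cachexia, so any such count is a larger share of its cohort than of 600.

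**Step 6. Any or severe?** Question, outcome and method of question 5 all point to any cachexia; the objective adds severe. The severity measure in question 3 has components but no threshold, so it cannot define a severe event as it stands.

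**The case against.** The strongest reply is that this is an article. It says that CT is used to measure lean body mass, so some derivation is evidently intended, and the route from scan to index and the handling of missing scans may stand in the full protocol or analysis plan. The questions are secondary, and the Discussion calls the work on inflammation explorative. Part of this stands: silence on missing scans would not be a finding by itself. But the article is not silent on the index. It states an exact measure with exact cut-offs and lists a different measurement. Lean body mass from a vertebral scan is not limb muscle per height squared, and the kg/m2 cut-offs do not carry over without a stated conversion.

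Three further objections stand, each against a stronger reading that a reader might infer:

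- *Cachexia at baseline and follow-up is misclassified generally.* It is not. Criterion (c) also requires weight loss above 2%, so sarcopenia alone is not cachexia, and (a) or (b) decides most of the pattern in Step 3.
- *Case-finding follows scan frequency, which follows disease activity and inflammation.* This needs a CT surrogate that the article does not state, and a link between scanning and disease that it does not state either. If (c) is simply not applied, no scan creates a case.
- *All of question 3 is biased.* Only its baseline regression uses the definition. Scans at follow-up cannot affect that regression, and the longitudinal severity outcome contains no muscle index.

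**Conclusion.** Criterion (c) cannot be applied as written; this follows from the text and needs no assumption. It is a rule fixed wrongly rather than a detail left out, because it helps to set the baseline outcome of question 3 and both the risk set and the event of question 5.

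Misclassification is conditional. It arises if a CT surrogate is used and a missing scan is read as not sarcopenic, and then only for patients with weight loss above 2% and up to 5% and BMI of at least 20. Its size cannot be derived from the document. The assumed inputs give anything from none (every patient has a usable scan) to 75 of 600, so no single number should be quoted as an estimate.

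The primary endpoint, the sample size and the longitudinal severity analysis are untouched. The severe/any wording is a smaller point: one objective sentence is out of line with the rest of question 5. The point should be settled before the cachexia analyses are run.

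**What to change.** 1. In criterion (c), replace the kg/m2 cut-offs with a cut-off valid for the CT measure and vertebral level actually used.
2. Analyse the baseline part of question 3 and all of question 5 with criteria (a) and (b), which do not depend on CT. Also apply the full (a)/(b)/(c) definition among patients with CT at baseline and, for question 5, at the visit concerned. Report both.
3. Reconcile the Clinical variables statement on baseline CT with Table 1.
4. Align the objective of question 5 with its question, outcome and method, or give a threshold for severe cachexia. The components listed under question 3 would need one before they could serve as an event.

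The cost is wording and coding, with no new scans. The downside is that cases meeting only (c) are not counted in the CT-independent analysis, and the full-definition analysis uses fewer patients. Reporting both shows how far the conclusions depend on (c).

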### Cancer related symptoms and the role of inflammation

In recent years there has been an increased interest among researchers to understand the correlation between the immune system and development of cancer and cancer-related symptoms. Inflammation is present in the majority of patients with advanced cancer [29], and it is therefore difficult in cross sectional studies to establish if inflammation is simply associated with severity of the cancer disease, or whether inflammation itself elicits symptoms and can be a target to reduce symptoms like pain, depression or cachexia [30].

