#### Development of cachexia and the role of inflammation

Up to 80% of patients with advanced metastatic cancer develop cachexia, and approximately 20 % of cancer deaths are attributed to cancer cachexia [37]. Cancer cachexia has a significant impact on patient morbidity as these patients often have reduced physical function, increased fatigue and psychosocial distress. According to a recent international consensus cachexia has been defined as a multifactorial syndrome characterized by an ongoing loss of skeletal muscle mass (with or without loss of fat mass) that cannot be fully reversed by conventional nutritional support and leads to progressive functional impairment [38]. In the consensus document, cachexia is described as a trajectory from early cachexia to late cachexia, and treatment should be assigned to patients according to the different stages. A longitudinal observational study is required to establish which factors predict both the cachexia syndrome and late cachexia.

The complete pathophysiology behind cachexia is still unclear. Most studies on molecular mechanisms have been performed on different animal models; studies in humans are scarce. Anemia, low serum albumin and increased inflammatory biomarkers such as CRP, TNF-α, soluble TNF-receptor 1 (sTNF-R1), IL-1, IL-6 and interferon (IFN)-gamma are observed in patients with cachexia [39]. Inflammatory markers such as TGFβ involved in development of bone metastases is probably also important in development of cachexia [40]. However, systemic inflammation is seen in a majority of patients with cancer, and not all of them develop cachexia therefore as for pain longitudinal studies are needed.

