#### Depression in patients with advanced cancer and the role of inflammation

Depression disorder contribute to reduced quality of life in patients with advanced cancer [41]. Depression disorder is common among cancer patients with a prevalence that varies from 5 to 30% between studies [42]. A particular challenge for assessment of depression in patients with advanced cancer is the somatic depression symptoms (fatigue, psychomotor retardation, appetite disturbance and sleep disturbance) which constitute 4 out of 9 diagnostic criteria for depression disorder. In patients with advanced cancer the somatic depression symptoms can result from depression, the cancer, treatment effects, or a combination of these factors [43].

In a cross-sectional study that also controlled for disease load, we demonstrated that by only using the 5 psychological depression symptoms for defining depression disorder, we could circumvent the challenge of the overlap between the somatic depression symptoms and symptoms of the cancer [44] [45]. However, our study was cross-sectional thus limiting the possibility to assess causality [44]. Studying the development of depression disorder and each of the depression symptoms over time with control for disease and treatment(s) can provide evidence-based guidance on how to best assess depression in patients with advanced cancer.

Patients with advanced cancer and depression disorder have more somatic symptoms including pain compared to non-depressed patients, but no appropriately designed studies to examine a possible causal relationship have to our knowledge been published. Clinically, a common observation is that long-lasting pain is associated with increased levels of depression symptoms. Still the direction of causality is not established and might be bidirectional. The relation between pain and depression has to be studied in a longitudinal design in order to better understand how they are related.

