*Statistical method*: Clinical variables (see previous chapter) and CRP will be included in a multivariate logistic regression model to predict potential factors for response to RT. The model will be adjusted by study centre. Regression diagnostics will be performed for all analyses adding interactions terms if necessary. Significant variables from the multivariable model will be presented as a response-score to determine the likelihood of response to RT. Second, we will perform analyses on inflammatory biomarkers and bone biomarkers correlated with response to RT. Only inflammatory biomarkers and bone biomarkers with levels of serum concentrations above the detection threshold and which have a variability between measurements will be analysed with a multivariate logistic regression model with response to RT as the dependant variable. Finally, an integrated regression model with response to RT including both the significant clinical variables and significant biological biomarkers will be conducted if appropriate based on results from the previous analyses.

**Research question 2:** Which inflammatory biomarkers are associated with change in pain intensity in patients with CIBP?

*Objective*: To investigate the correlation between pain intensity and inflammation. Patients included in the PRAIS study all have CIBP and will receive a standardized intervention expected to give pain relief in about 60% of the patients. This study can explore if there is a longitudinal relationship between changes in pain intensity and the detected level of inflammatory biomarkers.

*Outcome*: Serum concentrations of inflammatory biomarkers as described above associated with changes in pain intensity as measured by average pain intensity and worst pain intensity last 24 h (NRS 0–11) for a maximum of 1 year follow-up.

*Statistical method*: Longitudinal data analysis with repeated measurements using a liner mixed effect model or generalized estimating equation (GEE).

**Research question 3:** Which inflammatory substances are associated with cancer cachexia?

*Objective*: To gain insight into the role of inflammation in cancer cachexia.

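### The Research question 3 baseline cachexia model names no tumour-type or disease-extent term, so differences between cancers can appear as marker–cachexia associations

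*Protocol article*

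**What the plan says.** In the protocol article, under Outcome and statistical analyses, RQ3 has the objective "To gain insight into the role of inflammation in cancer cachexia". Its statistical method has two steps. The first is a cross-sectional analysis at baseline by "a logistic regression with cachexia as outcome, and the various inflammatory markers as explanatory variables". In the second, "we will investigate the association between changes in inflammatory markers over time and cachexia severity using mixed linear modelling". Neither step names a clinical covariate or a centre term.

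Research question 1 (RQ1), in the same section, is specified differently: "Clinical variables (see previous chapter) and CRP will be included in a multivariate logistic regression model", followed by "The model will be adjusted by study centre".

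Three other places bear on the point:

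- Background, Cancer related symptoms and the role of inflammation: because inflammation is present in most patients with advanced cancer, "it is therefore difficult in cross sectional studies to establish if inflammation is simply associated with severity of the cancer disease" or is itself a cause of symptoms. Cachexia is among the symptoms listed.
- Background, Development of cachexia and the role of inflammation: "systemic inflammation is seen in a majority of patients with cancer, and not all of them develop cachexia".
- Background, Depression in patients with advanced cancer: the group's earlier work is introduced with "In a cross-sectional study that also controlled for disease load". The same subsection later asks that marker studies of depression control for disease.

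The inclusion criteria accept any verified cancer, haematological malignancies included. Clinical variables lists tumour diagnosis, time since diagnosis, metastases other than bone, age and gender as recorded at inclusion and marked for the primary analysis.

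**The concern.** Tumour type and disease extent can plausibly raise circulating markers and, separately, the chance of wasting. In a cohort that mixes all cancers, a marker unrelated to cachexia among patients with the same tumour and the same spread can still correlate with cachexia overall, because it identifies the cancers in which wasting is more common. A logistic model with markers as its only explanatory variables cannot tell these two situations apart.

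This is the weakness that the Background attributes to cross-sectional work. What is at stake is how the RQ3 baseline odds ratios are read. The objective speaks of a role for inflammation, and the Discussion looks ahead to using biological factors to choose patients for treatment against cachexia. An association that reflects case mix would support neither use.

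**Working it through.** **Plan's own figure.** There is none for RQ3. The sample-size rule (10 × 29 variables = 290, which reproduces) and the final 600 are set for RQ1. The check below takes only n = 600 from the article. Every confounder strength is an assumption.

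**Model.** A binary disease factor G (a tumour group, or extensive disease) has prevalence g. It shifts a marker with unit SD within groups by δ, and it sets cachexia risk at p1 (G present) or p0 (G absent). The marker has no direct effect. The test is a two-sided Wald test at 0.05.

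**Assumption set A** (2000 data sets per setting): g = 0.40; cachexia 60% v 30%, or 55% v 40%; δ = 0.3, 0.5, 0.8.

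**Assumption set B** (1000 data sets per setting): g = 0.50; overall cachexia about 30%; G-to-cachexia odds ratio 1.5, 2 or 3; δ = 0.3, 0.5, 0.8.

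**Closed-form check**, set A, 60% v 30%, δ = 0.5:

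- Overall cachexia: 0.4 × 0.6 + 0.6 × 0.3 = 0.42.
- Share with G among cachectic patients: 0.24 / 0.42 = 0.571. Among the others: 0.16 / 0.58 = 0.276.
- Mean marker difference: 0.5 × (0.571 − 0.276) = 0.148.
- Marker variance within outcome groups: 1 + 0.25 × (0.42 × 0.571 × 0.429 + 0.58 × 0.276 × 0.724) = 1.055.
- Spurious log odds ratio: 0.148 / 1.055 = 0.140, so the odds ratio is about 1.15.
- Standard error: 1 / √(600 × 0.42 × 0.58 × 1.055) = 0.081, so z ≈ 1.74.
- Probability of significance: P(Z > 1.96 − 1.74) ≈ 41%. The simulation gave 40%.

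**Marker-only model, null marker significant:**

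| Assumption | δ (SD) | Simulated | Same formula |
|---|---|---|---|
| A, 60% v 30% | 0.3 | 16% | 19% |
| A, 60% v 30% | 0.5 | 40% | 41% |
| A, 60% v 30% | 0.8 | 77% | 76% |
| A, 55% v 40% | 0.3 | 8% | 8% |
| A, 55% v 40% | 0.5 | 14% | 14% |
| A, 55% v 40% | 0.8 | 26% | 26% |
| B, odds ratio 1.5 (weakest) | 0.3 | 6% | 6% |
| B, odds ratio 3 (strongest) | 0.8 | 60% | 61% |

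The simulated spurious odds ratios per SD were 1.09, 1.15 and 1.26 for set A at 60% v 30%, and ran from 1.03 to 1.20 across set B.

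**With G in the model:** significance in 4% to 6% of data sets in both sets, and an odds ratio of 1.00 in set B.

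These rates are for one marker and one binary confounder. Table 2 of the article lists more than 25 inflammatory markers, and the text does not say whether they enter together or singly. The rates do not carry over to a joint model, though the mechanism remains.

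**The case against.** The strongest reply is that the text does not fix an unadjusted model. It names the outcome and the exposures of interest in half a sentence and nowhere says that nothing else will enter. This is a journal article, and covariates for secondary models are often left to a fuller document. RQ2, RQ4, RQ5 and RQ6 also list no adjustment variables, even though the Background wants disease controlled in the depression work. On that showing, silence is weak evidence of exclusion.

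This stands in part. A reader might infer that the investigators have decided against adjustment. The article does not show that, and a document not at hand may add covariates. But RQ3 does more than name a class of model, as RQ4 and RQ6 do. It lists its explanatory variables, in a section presented as a detailed overview, where RQ1 spells out both clinical variables and centre. As stated, that list fits poorly with the article's own account of the problem.

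A second reply is that RQ3 asks about association, that the Discussion calls the inflammation work explorative, and that the article's remedy for cross-sectional limits is longitudinal data: RQ3's second step, and RQ5's Cox model in patients free of cachexia at baseline. This lowers the severity and rules out saying that the RQ3 objective goes unanswered. It does not remove the point. The second step concerns severity, not cachexia status, and names no disease covariates. RQ5 asks a different question, and the baseline odds ratios would still be reported.

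A third reply is that the magnitude is wholly assumed. That is correct.

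**Conclusion.** The concern holds in a limited form. As stated, the RQ3 baseline logistic model has the inflammatory markers as its explanatory variables and no tumour-type or disease-extent term, so differences in case mix can appear as marker–cachexia associations.

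The size is unknown from the documents. Over the assumptions tried, the false-positive rate for a null marker runs from 6%, which is close to nominal, to 77%. A reader might infer that null markers will turn out significant. The calculations do not support that: in five of the six settings in set A the rate is below one half, and with weak confounding the harm is slight. What does hold throughout is that the bias runs upwards when the disease factor raises both marker and cachexia risk, and that including the factor restores about 5%.

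This is an analysis that should be improved before the RQ3 results are interpreted. It does not touch the primary analysis.

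**What to change.** State that the RQ3 baseline logistic model includes, alongside the markers, tumour diagnosis, presence of metastases other than bone, time since diagnosis, age, gender and study centre. Report the adjusted odds ratio as the RQ3 baseline result and label the marker-only result as descriptive.

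Add steroid use and current anti-cancer treatment in a sensitivity analysis only. Wasting may influence both, so their place in the main model is debatable. Performance status is better left out for a similar reason, since the Background describes functional impairment as a consequence of cachexia.

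The cost is a sentence or two in the analysis plan and some degrees of freedom. Tumour diagnosis has many categories and the marker list is long, so diagnoses should be grouped in advance to limit the loss. No new data are needed, because all these variables are available at baseline. If a fuller analysis plan already adjusts this model, it is enough to say so and name the covariates.
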